***Aim 1***		
Recruitment rate	Number of mothers per week recruited	Mean 2 participants/week
Retention rate	% of mothers with data at follow-up	> 80% of mothers with follow-up data
Perceived usefulness	Usefulness subscale of mHealth App Usability Questionnaire	Mean score of < 3
Processing time	Time from initial contact until study enrollment	Mean time is < 1 week
Post-intervention questionnaire completion time	Time to complete post-intervention questionnaires	Mean of < 60 min to complete
Follow-Up questionnaire completion time	Time to complete follow-up questionnaires	Mean of < 60 min to complete
Questionnaire completion	% of missing data among program completers	> 80% of data is present among mothers who completed follow-up
Treatment adherence	Logging onto BEAM App and/or attending weekly group telehealth session	Participation in > 50% of program weeks via logging onto BEAM App or attending weekly group telehealth session
Safety	Adverse events from the BEAM program or assessments	No adverse events reported
***Aim 2***		
Treatment response	Comparison between groups	Significant group difference in primary clinical outcomes (depression and anxiety)
Treatment effect	Estimate of effect size and variance for future sample size calculations	Data on all relevant variables
Baseline severity moderation	Comparison of those with low versus high baseline scores on the PHQ-9 and GAD-7	Significant group difference

#### Aim 1

Back-end App data, collected via Google Analytics and Firebase, will be used to assess recommended mHealth engagement variables [46, 47]: (a) number of logins and sessions to the BEAM app, (b) number of forum posts, (c) time spent on the BEAM app and on the forum, (d) number of videos watched/time spent watching videos, and (e) number of weeks between first and last engagement with the app. Weekly telehealth group session attendance (yes/no) will be compiled by the clinical team. Analytics and group attendance data will also be used to assess retention (number of weeks completed) and completion (participating in > 50% of program weeks by either logging onto the BEAM app or attending the weekly group telehealth session). Finally, the mHealth App Usability Questionnaire (MAUQ) [48] will assess participants’ views on the BEAM program.

#### Aim 2

Data on maternal depression (PHQ-9) and anxiety (GAD-7) will be used to estimate effect size for a future large-scale RCT and to assess preliminary mean change in variables of interest across assessment timepoints. The PHQ-9 includes [35] nine items which will ask mothers the severity of their depressive symptoms during the past 2 weeks. The PHQ-9 has high internal consistency (*α* = 0.88) [49]. Anxiety symptom severity will be assessed using the GAD-7, a seven-item measure which will ask mothers their degree of anxiety symptoms over the past 2 weeks. The GAD-7 has excellent internal consistency (*α* = 0.92) [36]. Items on both scales are scored on a 4-point Likert scale ranging from 0 (“Not at all”) to 3 (“Nearly every day”) where higher summative scores suggest more problematic symptoms.

Additional questionnaires will assess maternal mental health (i.e., Patient Reported Outcomes Measurement Information System [PROMIS] Anger [PROMIS-A] [50] and Sleep Disturbance [PROMIS-SD] [51] subscales, Alcohol Use Disorder Identification Test [AUDIT] [52] Cannabis use Disorder Identification Test – Revised [CUDIT-R] [53], Substance Use Motives Measure—Coping Subscales [SUMM] [54], and Depression Severity Index—Suicidality Subscale [DSI-SS] [43]), parenting (i.e., Parenting Stress Index – Short Form [PSI-SF] [40], Perceived Maternal Parenting Self-Efficacy [PMP S-E] [55], and the Parenting Scale—Overreactivity Subscale [56], Couples Satisfaction Inventory 4-Item [CSI-4] [57]), and child outcomes (i.e., Ages and Stages Questionnaire: Social-Emotional Challenges – 2 [ASQ:SE-2] [58], Pediatric Quality of Life Inventory [PedsQL] [59], and Infant Behavior Questionnaire – Revised – Very Short Form—Effortful Control Subscale [IBQ-R-VS] [60]).

Data on sociodemographic characteristics will be collected in the pre- and/or post-intervention questionnaires including (a) maternal demographics (e.g., age, marital status, highest level of education, ethnicity, employment, depression persistence, anxiety persistence), (b) child demographics (e.g., child sex, age of child), and (c) household demographics (e.g., number of adults and children in the household, annual household income, community type).

Other variables known to impact adult mental health and child development will be collected including the Adverse Childhood Experiences (ACEs) Questionnaire, the author-compiled Recent Stressful Experiences Questionnaire (RSE; developed based on recommendations from the JPB research network on toxic stress at Harvard’s Center on the Developing Child) [61], and the author-compiled Emergency Health and Social Service Utilization Questionnaire.

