### Objectives {7}

#### Aim 1

To examine the feasibility of the BEAM program when delivered by a community agency. Feasibility indicators include recruitment rate, retention rate, and perceived usefulness of BEAM, for example.

#### Aim 2

To assess preliminary implementation elements of the BEAM program to estimate effect size and variance for future sample size calculations (treatment effect) and compare the BEAM program to SOC [28] in primary clinical outcomes including maternal depression and anxiety (treatment response).

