### Outcomes {12}

Pre-specified success criteria are identified in Table 3. All feasibility indicators will be dichotomized into success or revise. “Success” indicates the protocol can move forward with a larger RCT with no/little revisions required, while “revise” suggests changes are needed prior to proceeding.

**Table 3 Tab3:** Feasibility indicators

Feasibility	Indictor	Criteria for success

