### Statistical methods {20a}

All analyses will be conducted using IBM Statistical Package for the Social Sciences (SPSS). Descriptive statistics will be computed for the total sample and between the two groups (i.e., BEAM and MoodMission) for demographics and outcome measures at pre-intervention.

#### Aim 1

Descriptive statistics from back-end App data, telehealth group attendance, and questionnaires (i.e., BEAM App-Based, BEAM Forum, BEAM Perceived Social Support, BEAM Zoom Telehealth Group, mHealth App Usability, and MoodMission App-Based) will be used to examine program feasibility, engagement, and acceptability.

#### Aim 2

Data on maternal depression (PHQ-9) [35] and anxiety (GAD-7) [36] will be used to estimate effect size and variance for future sample size calculations. Preliminary analyses will also examine treatment effects on outcomes of interest (e.g., depression, anxiety). A longitudinal analysis of covariance, using linear mixed modelling, will be conducted to preliminarily test treatment effects on outcomes of interest. Treatment effects will be tested using two-way interactions between time and group assignment. Baseline moderation by symptom severity will be assessed to determine whether the BEAM program helps reduce symptoms for mothers with higher levels of depression and anxiety at pre-intervention compared to MoodMission. An *α* of 0.05 will determine statistical significance. Aggregate variables will be computed, by converting each measure to a standardized *z*-score then taking the average. Results will be reported as means and 95% confidence intervals for all comparisons. Bonferroni corrections are considered very conservative [64], and it has been suggested that correction may not be necessary, particularly if the study purpose is exploratory [65].

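### Table 3 lets an unpowered significance test, with no time point or direction, decide success or revise for treatment response, in a trial whose tests are otherwise called preliminary and exploratory

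*Protocol article*

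**What the plan says.** Outcomes {12} introduces Table 3 as a list of pre-specified criteria and states: "All feasibility indicators will be dichotomized into success or revise". Success, it explains, "indicates the protocol can move forward with a larger RCT with no/little revisions required"; revise means that changes are needed first. In the Aim 2 part of Table 3, the treatment-response row is met by a "Significant group difference in primary clinical outcomes (depression and anxiety"). Objectives {7} describes the same comparison with SOC as being "in primary clinical outcomes including maternal depression and anxiety (treatment response").

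Statistical methods {20a} supplies the test. An alpha "of 0.05 will determine statistical significance". On the model: "Treatment effects will be tested using two-way interactions between time and group assignment". On multiplicity, it calls Bonferroni very conservative and adds that "it has been suggested that correction may not be necessary, particularly if the study purpose is exploratory". On reporting: "Results will be reported as means and 95% confidence intervals for all comparisons".

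Trial design {8} sets three assessments: pre-intervention (T1), post-intervention (T2) and 6-month follow-up (T3). Sample size {14} says that a sample size calculation is not appropriate for a pilot. It takes 30 per group from prior recommendations and raises this to 40 for attrition. Blinding {17a–b} says the data analysts are not blinded.

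**The concern.** Two parts of the plan use the same test for different purposes. Statistical methods {20a} treats it as exploratory and on that ground argues that correction may be unnecessary. Table 3 treats it as a pre-specified pass mark. An exploratory rationale suits estimation. It does not suit a binary verdict triggered by p < 0.05, least of all in a trial that was not sized for that test.

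The pass mark also leaves three things open:

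- **Time.** Nothing says whether T2, T3 or an overall time-by-group test decides.
- **Direction.** A difference in favour of MoodMission satisfies the words.
- **Outcomes.** The word *and* points to both PHQ-9 and GAD-7, but the rule is not stated as a rule.

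The same data could therefore be called success or revise, and unblinded analysts could settle the reading after seeing the results. On the strictest natural reading the larger risk is the reverse of a false positive: a programme that works would often be marked for revision because the test had little chance of succeeding.

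**Working it through.** **The plan's own figures.** The only precision figures in Sample size {14} concern proportions with n = 40. They reproduce from 1.96·√(p(1−p)/n): for p = 0.80, 1.96·√(0.16/40) = 12.4%; for p = 0.50, 1.96·√(0.25/40) = 15.5%. The document gives no error rate or power for treatment response, so there is nothing to reproduce there.

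**Inputs.** From the document: alpha 0.05 per test, two outcomes, two post-baseline times, 1:1 allocation, 30 per arm as the target. Assumed: two-sided tests (in line with the 95% intervals), correlation ρ between the PHQ-9 and GAD-7 test statistics, and likewise between T2 and T3. The document gives neither correlation, so a range is shown.

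**Null programme, one named time point.** With P(either) = 1 − P(|Z₁| < 1.96 and |Z₂| < 1.96), and P(both) = 2 × 0.05 − P(either):

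| ρ between outcomes | either | both |
|---|---|---|
| 0 | 9.75% | 0.25% |
| 0.3 | 9.5% | 0.5% |
| 0.5 | 9.1% | 0.9% |
| 0.8 | 7.8% | 2.2% |

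**Null programme, other readings.** These come from simulation, 1,000,000 draws per setting, with both correlations at 0.5 unless stated:

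- One overall (2-df) time-by-group test per outcome: both 0.8%, either 9.1%.
- Both outcomes at the same time, T2 or T3: 1.8%.
- Any of the four contrasts (two outcomes × T2, T3): 16.1%; 17.7% with both correlations at 0.3 and 12.0% with both at 0.8. With independence it is 1 − 0.95⁴ = 18.5%.

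**Direction.** By symmetry about half of these null successes favour MoodMission. Requiring a difference in favour of BEAM lowers any-of-four from 16.1% to 8.1%.

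**An effective programme.** Assume a true effect of 0.5 SD on both outcomes, 30 analysed per arm, one time point and no baseline adjustment. The test statistic has mean d·√(n/2) = 0.5·√15 = 1.936.

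- One outcome: 1 − Φ(1.960 − 1.936) + Φ(−1.960 − 1.936) ≈ 49%.
- Either, ρ = 0.5: 65.7%.
- Both, ρ = 0.5: 2 × 49.07% − 65.7% ≈ 32.4%.
- Both, over ρ = 0.3 to 0.8: 29% to 39%.

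Adjusting for baseline helps. An assumed baseline correlation of 0.5 leaves 1 − 0.25 of the variance, equivalent to 30/0.75 = 40 per arm; both then succeed about 45% of the time at ρ = 0.5.

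**The case against.** The strongest reply is that the criterion is clearer than it is made out to be. The Table 3 row gives a closed list of two outcomes joined by *and*, and on that reading false positives are not inflated and no correction is needed. This stands, and 0.9% confirms it. It also exposes the other problem: the chance of success under a moderate true effect is low.

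Second, treatment response is a secondary outcome in the registration table, the tests are called preliminary, and no rule makes this row alone decide progression. That stands too. A reader might infer that a false success here amounts to an efficacy claim or by itself launches the larger trial. The documents do not say so.

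Third, multiplicity was discussed openly, and details such as the deciding time point are often left to an analysis plan. Leaving details to that plan would be no fault. But the protocol itself fixes the pass mark, the alpha and the stance on correction, and the conflict lies among those statements.

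Two stronger readings should be resisted. A reader might take 16% as the error rate of the rule. It requires *either* in place of *and*, separate T2 and T3 contrasts, and correlations near 0.5. The plan does name a test family, the time-by-group interaction, and one overall test per outcome caps the *either* figure at about 9%. A reader might also count the additional questionnaires in Outcomes {12} as further chances to succeed. The Table 3 row is confined to depression and anxiety, so they do not enter this verdict.

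**Conclusion.** The point holds as a defect in the decision rule, not as a claim of large false-positive inflation. The success criterion for treatment response conflicts with the exploratory status given to the same tests and with a sample size that rests on no power calculation.

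On the natural reading, both outcomes at one time point, null success is about 0.9% (0.5% to 2.2% for assumed correlations of 0.3 to 0.8). An assumed 0.5 SD effect with 30 per arm and correlation 0.5 succeeds about 32% of the time, so roughly two times in three a programme of that benefit would be marked revise. If either outcome suffices, null success is about 9%, and 12% to 18% if T2 and T3 are tested separately as well. On any of these readings the missing direction lets a result against BEAM count as success.

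The effect size, the correlations, two-sidedness and the absence of baseline adjustment are assumptions. A larger effect or strong baseline adjustment would raise the 32%. They would not supply the missing time point or direction.

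**What to change.** Take the word significant out of the treatment-response criterion in Table 3. Base the row on the estimated BEAM minus MoodMission difference in PHQ-9 and in GAD-7, each with its 95% confidence interval. Statistical methods {20a} already promises these, and they serve the stated aim of informing the next sample size.

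If the sponsor prefers to keep a significance rule, the row should state the deciding time point (or the overall interaction test), that the difference must favour BEAM, and whether both outcomes or either is required. Alpha needs to be split only if either suffices; if both must be significant, 0.05 for each is enough. The exploratory argument against correction should then not be applied to this row.

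The cost is a few sentences in Outcomes {12} and Statistical methods {20a}, with no extra participants or data. The one loss under the preferred change is that this row no longer gives a verdict based on significance.

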### Eligibility criteria {10}

Participants must (a) identify as a mother (i.e., biological, adoptive, foster, step-mother, or another type of woman-identifying primary caregiver), (b) have a child between 6 and 18 months old at recruitment, (c) be 18 years old or above, (d) reside in Manitoba, Canada, with access to a cellular network, (e) score > 9 on the Patient Health Questionnaire-9 Item (PHQ-9) [35] and/or the General Anxiety Disorder-7 Item (GAD-7) [36], (f) complete a psychodiagnostic mental health assessment (Mini International Neuropsychiatric Interview; MINI) [34] and pre-intervention survey before randomization, (g) meet criteria for a major depressive episode and/or anxiety disorder (i.e., panic disorder, agoraphobia, social anxiety disorder, or generalized anxiety disorder) as assessed by the MINI, (h) be available to attend weekly telehealth groups, and (i) be comfortable understanding, reading, and speaking English. Exclusion criteria include: (a) a suicide attempt in the past year, (b) self-harm in the past 6 months, and/or (c) clinically significant psychotic symptoms, posttraumatic stress disorder, or alcohol/substance use disorder (identified on the MINI 34) which, based on clinical judgement, would make it unlikely for the individual to attend weekly group telehealth sessions and/or make treatment gains. The BEAM and MoodMission programs are not suitable to treat these acute mental health needs and as such mothers deemed ineligible for these reasons will be provided with local mental health resources more appropriate for their needs.

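### Baseline-severity moderation is defined as a low-versus-high comparison of summed scores; testing arm by the continuous T1 score would avoid losing about 36% of the moderator information

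*Protocol article*

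**What the plan says.** Baseline severity moderation is one of three secondary outcomes in the registration data set and has its own row under Aim 2 in Table 3 (Outcomes {12}). The indicator is "Comparison of those with low versus high baseline scores on the PHQ-9 and GAD-7", and success means that a difference between groups reaches significance. The text introducing Table 3 says that the success criteria are pre-specified.

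Statistical methods {20a} describes the purpose: "Baseline moderation by symptom severity will be assessed to determine whether the BEAM program helps reduce symptoms for mothers with higher levels of depression". The same sentence covers anxiety and makes MoodMission the comparator. The modelling framework is stated in the same section: "A longitudinal analysis of covariance, using linear mixed modelling, will be conducted to preliminarily test treatment effects on outcomes of interest". Treatment effects are tested there through the interaction of time and group. On the threshold it says "An *α* of 0.05 will determine statistical significance". It does not say whether severity enters as a score or as two groups.

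On the scores themselves, Outcomes {12} says "Items on both scales are scored on a 4-point Likert scale ranging from 0" to 3, and that "higher summative scores suggest more problematic symptoms". Nine items give a PHQ-9 range of 0 to 27, and seven items give a GAD-7 range of 0 to 21.

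**The concern.** The moderator is a graded score measured before randomisation in every mother. The only operational definition in the article turns it into two groups. Mothers just either side of the cut are then treated as different, and all mothers on one side as the same. No clinical reason for grouping is offered, and the planned mixed model could carry the score as it stands.

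At stake is a success-or-revise verdict that depends on significance, in a trial of at most 80 mothers. An interaction test is already weak at that size, and a split makes real moderation harder to find. The estimate it gives also depends on where the cut falls.

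**Working it through.** **The plan's own figures.** No power or effect size is given for moderation. The only precision figures are the confidence half-widths in Sample size {14}, and they reproduce with 40 BEAM mothers: 1.96 × √(0.8 × 0.2 / 40) = 0.124 and 1.96 × √(0.5 × 0.5 / 40) = 0.155. They do not bear on moderation.

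**Inputs from the protocol.** 80 mothers recruited, 1:1 allocation, α = 0.05 (taken as two-sided). With the stated 30% attrition, 80 × 0.70 = 56 remain. The stated target of 30 per group gives 60.

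**Inputs assumed.** One post-baseline score; standard normal baseline x; g = arm; y = 0.5x + 0.3g + b·g·x + e, with residual SD 0.87; split at the median. The slope difference b is in outcome SD per baseline SD.

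**Step 1: information lost.** For a cut at c that leaves a fraction q below it, the relative efficiency is φ(c)² / [q(1 − q)], where φ is the standard normal density. At the median, φ(0)² = 1/(2π) and q(1 − q) = 1/4, so the efficiency is 2/π = 0.637 and 36.3% is lost. Uneven cuts lose more: 46% at 75/25 and 51% at 80/20.

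**Step 2: what that means for power.** If full-score power is Φ(d − 1.96) + Φ(−d − 1.96), the split replaces d by d × √0.637 = 0.798d. At 50% power d = 1.96; 0.798 × 1.96 = 1.564, and Φ(1.564 − 1.96) = 34.6%.

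| Power, full score | Power, median split | Loss (points) |
|---|---|---|
| 20% | 14.5% | 5.5 |
| 30% | 20.9% | 9.1 |
| 50% | 34.6% | 15.4 |
| 70% | 50.9% | 19.1 |
| 80% | 60.8% | 19.2 |
| 90% | 73.4% | 16.6 |

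The loss peaks at 19.4 points, where full-score power is about 76%.

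**Step 3: simulation with the continuous baseline kept as a covariate** (only the interaction uses the split):

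| N | b | Full score | Split | Loss (points) |
|---|---|---|---|---|
| 56 | 0.2 | 13% | 10% | about 3 |
| 80 | 0.2 | 17% | 12% | about 5 |
| 56 | 0.3 | 24% | 17% | 7 |
| 56 | 0.5 | 53% | 36% | 17 |
| 60 | 0.7 | 83% | 61% | about 21 |
| 80 | 0.7 | 93% | 77% | 16 |

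Finite samples and simulation error put the largest loss a little above the analytic 19.4.

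**Step 4: simulation with the split replacing the baseline score altogether.** Losses for b from 0.3 to 0.7 are then about 8 to 31 points, for example 83% against 52% at N = 60 and b = 0.7. The extra loss arises because the slope within each half goes into the residual. At b = 0.7 the arm slopes are 0.5 and 1.2, so the added variance is 0.363 × (0.5² + 1.2²)/2 = 0.31 on 0.87² = 0.76. Overall efficiency is 0.637 × 0.76/(0.76 + 0.31) = 0.45.

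**The case against.** Four points are fairly made against this concern.

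- **The split may not be the model.** Table 3 is a one-line summary, section 20a names no groups, and estimates at low and high values are a usual way to display a continuous interaction. It is true that section 20a leaves the form open, so a reader should not infer that a dichotomised term is fixed as the analysis. But Table 3 is the only operational definition given, it speaks of comparing mothers with low scores against mothers with high ones, and nothing in section 20a overrides it.
- **The cost is easily overstated.** A reader might infer a power loss of up to about 31 points. That requires the split to remove the continuous baseline from the model, and an analysis of covariance would ordinarily keep it. It also requires the baseline slope to rise from 0.5 to 1.2 between arms, and nothing in the protocol points to an effect of that size. This objection stands, and the figures in the verdict respect it.
- **Other supporting arguments are weak.** A reader might add that entry restricts the range of severity. The criterion is "score > 9 on the Patient Health Questionnaire-9 Item (PHQ-9) [35] and/or the General Anxiety Disorder-7 Item (GAD-7"), so a mother can enter on one scale with a low score on the other. A reader might also fault the absence of a cut-point, but an article may leave that detail to the analysis plan.
- **The consequence is limited.** A reader might infer that a cut-dependent moderation estimate feeds the next trial's sample size. Table 3 assigns that purpose to the separate treatment-effect row. The protocol calls its testing of treatment effects preliminary, and at b = 0.3 power is low even with the full score (24% at N = 56).

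What remains is that the stated definition is less efficient than an alternative that the planned model already allows.

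**Conclusion.** The point holds as a modest one. Table 3 defines moderation by a low-versus-high comparison judged on significance, and section 20a does not commit to the continuous score. A median split of a normal score loses about 36% of the moderator information. With baseline kept as a covariate and 56 to 80 mothers, the cost is about 7 to 21 points of power for slope differences of 0.3 to 0.7 SD per SD, and about 3 to 5 points at 0.2.

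The information loss depends only on a normal score and a median cut. The power figures also depend on slopes that the protocol does not give, on a single post-baseline outcome, and on a two-sided test. They show the order of the loss and do not predict this trial's power. The change is worth making because it is nearly free; the indicator is secondary and exploratory.

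**What to change.** In Table 3 and Statistical methods {20a}, define the indicator as the interaction of arm with the continuous T1 score in the planned linear mixed model, combined with time in the same way as for the treatment effect. Use the T1 PHQ-9 for depression and the T1 GAD-7 for anxiety. Report the interaction with its 95% CI, together with the model-estimated BEAM-minus-MoodMission difference at two or three scores named in advance. Keep any low/high table as descriptive only.

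The cost is a change of wording in two places and one model term in SPSS, with no new data. The small downside is that a linear interaction is assumed; a plot of residuals against the T1 score can check this.
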